##### d) Study participation recorded on discharge summary

The project officer will provide brief information regarding the participants' engagement in the trial into the area health service's online discharge summary system. This information will be communicated to GPs and other relevant health professionals upon the participant's discharge from hospital, in order for these services to support the participants' ongoing care, and for this study, their quit attempt in the community setting [27,28].

Additionally, participants allocated to the intervention condition will be offered the following supports to commence upon discharge:

#### 'Additional' intervention component

##### e) NRT

Participants will be offered up to 12 weeks free NRT [50-52]. An NRT protocol for this trial will be developed based on a combination NRT algorithm [53], the area health services' NRT protocol [30] and the product disclosure information for the NRT provided in this trial. Patch (21, 14 and 7 mg), lozenge, gum (2 and 4 mg), and inhaler (10 mg) will be prescribed according to the study NRT protocol, and based on a nicotine dependence assessment [54] and patient preferences. Combination therapy (patch plus adjunctive) will be recommended for all smokers. For those who smoke > 20 cigarettes per day, 2 mg gum or lozenge, or 10 mg inhaler will be offered to manage acute craving. Tapering of NRT dose will not be explicitly advised, but dosage and frequency of use will be closely reviewed during fortnightly telephone support.

On the day of recruitment, a project officer will send an email notification of the NRT prescription to the participant's Chief and Junior Medical Officer should there be any unknown medical concern. An initial 2 week supply of NRT will be provided to the patient at discharge. Subsequent supplies of NRT will be mailed fortnightly at the completion of the fortnightly telephone support call (below), in which daily cigarette consumption, nicotine withdrawal symptoms and patient preferences will be reviewed.

##### f) Community smoking cessation support groups

Referral will be offered to smoking cessation support groups developed in conjunction with allied health staff in local community mental health services, and delivered by staff in those services [55]. A project officer will complete a referral form for the participant and email it to the appropriate community mental health service (based on local government area) upon the participant's discharge from hospital. Group facilitators will contact participants to complete an initial screening interview and provide details of the group program. Groups will run on a rotating basis of one, one hour group for four weeks, and will follow an informational, group-oriented support and skills training format, with no specific psychological or behavioural intervention [56,57]. Content will be tailored to smoking and mental illness, with topics covered including: understanding nicotine addiction and withdrawal, smoking habits and triggers, benefits of quitting, effective use of NRT, illness management and interaction with medications, and quit strategies.

##### g) Proactive Quitline referral

The NSW Quitline (funded by the Cancer Institute, NSW) [45] is a confidential telephone based service designed to help smokers to reduce or quit tobacco smoking. With the consent of participants, the project officer will complete a proactive NSW Quitline referral form at the completion of the baseline interview, and fax to Quit NSW upon the participant's discharge from hospital. The Quitline will call the participant according to the time and day suggested by the participant on the form, within one week of referral. The telephone service typically involves 6 calls, and a follow-up call conducted three months following the participants' elected quit date, with content including: nicotine dependence; quit strategies; relapse prevention; and information on cessation products and services [45].

##### h) Fortnightly telephone support

For all intervention participants, support calls will be conducted by a telephone counsellor at three days, and one week post discharge [58]. If participants elect any of the 'additional' intervention supports, these calls will continue fortnightly for as long as the participant is engaged with the intervention (up to 16 weeks total). Each call will follow a predefined script as developed by the research team. Topics covered include: uptake, usage, problems and effectiveness of intervention supports (NRT, Quitline, community smoking cessation support groups), fortnightly review of NRT dosage, assistance with NRT use, monitoring and managing nicotine withdrawal symptoms, daily cigarette consumption, techniques to improve smoking outcomes, and general psychological support and encouragement. If participants are receiving study NRT, these fortnightly telephone support calls will act as a means for project officers to monitor NRT use, dosage and side effects, and to subsequently mail an appropriate fortnightly supply of NRT.

#### Intervention personnel, recruitment and training

Recruitment will be conducted by a registered Health Psychologist and several project officers with four year undergraduate Psychology degrees. Prior to commencement of recruitment, all recruitment staff will complete the area health services' mandatory 2-day mental health training, concerned with ensuring occupational health and safety when working in the hospital environment. All recruitment staff will be trained by a senior member of the research team and psychologist undertaking recruitment in conducting the baseline interviews and brief motivational interviewing, including the conduct of mock interviews, and sitting in on patient interviews.

The fortnightly telephone support service will be provided by a registered nurse (and undergraduate psychology student), experienced with patient contact and managing patient issues. The interviewer will undergo project specific training and will assist in the development of the support protocols and content.

Outcome data will be collected by blind telephone interviewers, independent of the study, with several years experience in conducting health related telephone based surveys, but no formal qualifications in psychology or social sciences. Interviewers will undergo project specific training where they will be briefed on the aims and methodology of the study. Details regarding project specific issues (including NRT and psychiatric medication) will be provided to ensure interviewers are able to prompt participants if they have any difficulty or confusion regarding outcome questions.

#### Treatment monitoring and fidelity

To ensure integrity of the intervention, members of the research team will have weekly contact with project officers, support call staff and follow-up telephone interviewers to ensure common issues or concerns are dealt with in a consistent and timely manner. The research team will also meet fortnightly with a working group comprising experienced mental health and drug and alcohol clinicians employed at the hospital site to raise and address any issues arising from working within the hospital and to discuss and gain insight into the best management of participants throughout the trial period. The research team will also meet quarterly with a larger advisory group to discuss the aims of the trial, ensure recruitment, follow-up and intervention delivery are occurring to the best standard possible, and to keep abreast of approach, consent and follow-up rates.

### Control condition

Participants allocated to the control condition will receive standard hospital nicotine dependence treatment only. This may include provision of NRT during hospitalisation and, upon discharge, up to 3 days provision of NRT and referral to 'Quitline'. Nicotine dependence treatment is known to be limited and to vary in this setting [36].

### Data collection and measures

#### Baseline

The baseline survey will be administered as a face to face interview by project officers, within the inpatient setting prior to the allocation of treatment condition, and will be of up to 1 hour duration for both groups.

#### Follow-up data collection

Follow-up data will be collected for both groups via blind telephone interview at one week, two months, four months and six months post discharge. To enable subsequent assessment of the effectiveness of the blinding, interviewers will be asked at the completion of the interview to indicate the treatment condition to which they believe the participant was allocated. If any participant experiences an acute phase of their psychiatric disorder during any of the follow-up phone interviews, they will be encouraged to contact their GP, psychologist or community mental health team. Participation will continue as normal unless the participant expresses severe psychological distress and/or they no longer wish to participate in the trial. To minimise attrition, notices will be mailed, one week prior the due date, to remind participants of each upcoming follow-up call [61]. The protocol for follow-up calls will comprise up to four weeks of call attempts, with at least 10 attempts made within the first seven days of the due date, and regular attempts thereafter. At the completion of the six month follow-up interview, a letter will be mailed to participants, notifying them that their participation is complete and thanking them for their contribution to the study.

#### Demographic information

Demographic details including level of education, employment status and whether the participant receives a government support pension will be collected during the baseline interview. At the completion of the baseline interview, additional demographic information will be obtained from the participant's medical record, by a Health Psychologist employed by the service, including participant's full name, medical record number, age, address at time of admission, gender, pregnancy status (if NRT is to be prescribed), marital status, Aboriginal or Torres Strait Islander cultural identification, date and length of current admission, smoking status on admission, nicotine dependence treatment provided during admission, primary and secondary mental health diagnoses, medications for mental and general health conditions, and date of most recent previous admission to the facility (if applicable).

#### Primary outcome measures

The primary outcomes of this trial relate to changes in participants' smoking behaviour. Smoking behaviour will be assessed at each of the four follow-up surveys (one week, two, four and six months) by: daily cigarette consumption; number and duration of quit attempts; and self-reported abstinence. Daily cigarette consumption and quit attempts are recognised and recommended outcome measures which are frequently used in this population [62,63]. When abstinence is reported, it will be verified by exhaled carbon monoxide (CO) levels using a MICRO+ Smokerlyzer, with a cut-off of < 10 ppm [42,63]. CO validation tests will be arranged during the follow-up surveys and will be conducted by a project officer within 3 days of the survey (with smoking status attained again at that time), in a public location convenient to the participant (eg. library) or, if not viable, conducted as a home visit following the institutional safety guidelines.

#### Secondary outcome measures

Secondary outcome measures will include: nicotine dependence, as measured by the Fagerstrom Test of Nicotine Dependence (FTND) [54]; changes in motivation to quit smoking, as measured by the Readiness and Motivation to Quit Smoking Questionnaire [64]; alcohol and other substance use, as measured by The Alcohol Use Disorders Identification Test (AUDIT) [65]; and mental well being, as measured by the Kessler Psychological Distress Scale (K10) [66].

#### Process measures

##### a) All participants

Details regarding participant uptake, use and perceived effectiveness of smoking cessation supports (provided by this trial or elsewhere) will be collected at each of the four follow-up time points (one week, two, four and six months post discharge) for participants in both conditions. In addition, the follow-up telephone interviewers will record data arising from the outcome of each follow-up telephone survey, including the time and date of all call attempts, call outcome (eg. engaged, answering machine, call partially complete, call complete or refusal), length of call, and the interviewer who conducted the call.

##### b) Intervention participants

For participants allocated to the intervention condition, more detailed information regarding uptake, use and effectiveness of the interventions provided by this trial will be collected systematically at each fortnightly telephone support call, including: intervention options elected at baseline, three day call and initial (one week) support call; whether the participant received their previous NRT allocation and details of its contents; usage of NRT, including type, dosage, and amount used per day; problems with and perceived effectiveness of NRT; smoking cessation support group attendance and effectiveness; number, date and effectiveness of calls received from Quitline; and any problems experienced with the intervention options or participation in the project. Additionally, information regarding the process and outcome of these calls will be recorded, including date and time of call attempts, call outcome (eg. engaged, answering machine, call partially complete, call complete or refusal) call duration, interviewer who conducted the call, and the total number of calls received by each participant in the intervention support phase.

##### c) Cost

This trial will provide a detailed evaluation of the costs to deliver the intervention. Cost will be determined by assessing: staff time associated with initial recruitment and follow-up support calls; NRT and other intervention materials (including self-help brochures); and phone and mail costs. Data for the use in calculation of costs will be collected through detailed records of baseline interview length, support call attempts and length, total NRT usage and associated mail costs.

### Sample size and detectable difference

A total of 200 participants (approximately 100 per group) will be recruited to the study (an estimated 70 per group at 6 month follow-up, assuming a 70% follow-up rate). This number is sufficient to conduct intention to treat analyses to examine intervention effectiveness (with 80% power and .01 level significance tests) in terms of differences on the continuous outcome measures (e.g., quit attempts, daily cigarette consumption, nicotine dependence) of the order of 0.51 standardised (effect-size) units, and 4.8 fold increases in point prevalence abstinence (e.g., treatment group, 24% abstinent, vs. comparison group, 5% abstinent). A previous, similar sized multimodal intervention study conducted among a mental health patient population demonstrated statistically significant differences (20% effect size or larger) between groups on continuous outcomes including reduction in daily cigarette consumption and nicotine dependence levels, but not for abstinence [21]. Due to the unique methodology and intensity of intervention employed in the current trial, it is uncertain whether this trial will have sufficient power to detect statistically significant differences in abstinence between the two conditions, however significant differences in other outcomes are achievable. It could be argued, based on the novel design of this trial, larger effect sizes may be achieved, but this remains speculative.

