#### Analysis

Data will be analysed using IBM SPSS Statistics for Windows (version 19.0). For the key smoking-related outcome variables, intention-to treat analyses will be conducted, together with subgroup analyses based on patterns of intervention uptake. For these analyses, missing data will be classified nonabstinent or as failing to achieve reduction. Odds ratios and associated confidence intervals (CI) will be reported, with the control group as the reference point (odds ratio = 1.00). For the continuous outcome variables (e.g., daily cigarette consumption), planned comparisons between follow-up points, from repeated-measures analyses of variance (ANOVAs), will be used to examine group differences in patterns of change. As a partial control for the number of statistical tests, the threshold for statistical significance will be set at p < 0.01. Among this population, evidence of satisfactory engagement with post-discharge support services and progressive changes in smoking behaviour are also considered highly desirable outcomes. The projected sample sizes should also be sufficient to allow an examination of correlations between selected participant characteristics and aggregate indices of engagement based on the various process measures.

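### The detectable difference of 0.51 SD at 80% power matches neither 70 nor 100 per group unless the analysis uses a within-person correlation that the plan does not state

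*Protocol article*

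**What the plan says.** The protocol article, *Sample size and detectable difference*, gives two group sizes. On recruitment: "A total of 200 participants (approximately 100 per group) will be recruited to the study". On retention: "an estimated 70 per group at 6 month follow-up, assuming a 70% follow-up rate". It then says the number suffices for intention-to-treat analyses "with 80% power and .01 level significance tests", with detectable differences "of the order of 0.51 standardised (effect-size) units, and 4.8 fold increases in point prevalence abstinence". The abstinence example is "treatment group, 24% abstinent, vs. comparison group, 5% abstinent".

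The *Analysis* section repeats the criterion: "the threshold for statistical significance will be set at p < 0.01". For the key smoking outcomes under intention to treat, it adds "For these analyses, missing data will be classified nonabstinent or as failing to achieve reduction". Continuous outcomes are to be compared by planned contrasts from repeated-measures ANOVAs that look at group differences in change over time. Neither section states the sidedness of the test or a within-person correlation.

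**The concern.** Power, significance level, group sizes and detectable difference are all printed in one paragraph, so they can be checked against each other. With the standard two-group formula they do not agree: 0.51 SD is too small for 70 per group and slightly too large for 100.

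This matters because daily cigarette consumption is among the primary outcomes, and the article already admits that power for abstinence is uncertain. The case that the trial is large enough therefore rests on the continuous outcomes, for which the article says significant differences are achievable. If the 6-month comparison is unadjusted with 70 per group, a true effect of 0.51 SD would be missed about one time in three, not one in five. A null result could then be read as stronger evidence against such an effect than it is.

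**Working it through.** **Inputs.** From *Sample size and detectable difference*: significance level .01, power 80%, d = 0.51, 100 per group recruited, 70 per group at 6 months, abstinence 24% against 5%. *Analysis* confirms the .01 level. I take the test as two-sided because no direction is stated, and also show the one-sided result. Normal quantiles: 2.576 (two-sided .01) and 0.842 (80% power).

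**Step 1. Group size that reproduces 0.51 SD.**
n = 2 × (2.576 + 0.842)² / 0.51² = 2 × 11.68 / 0.2601 ≈ 90 per group. The exact noncentral t calculation gives 92.

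**Step 2. What the two stated group sizes give.**
Power = Φ(0.51 × √(n/2) − 2.576); detectable difference = 3.418 × √(2/n).
- n = 70: 0.51 × √35 = 3.017, so power = Φ(0.441) = 67.0% (t: 65.7%).
- n = 100: 0.51 × √50 = 3.606, so power = Φ(1.030) = 84.9% (t: 84.1%).

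| Analysed per group | Power for 0.51 SD, normal / t | Difference detectable with 80% power, normal / t |
|---|---|---|
| 70 | 67.0% / 65.7% | 0.578 / 0.585 SD |
| 90 | 80.1% / 79.2% | 0.509 / 0.514 SD |
| 100 | 84.9% / 84.1% | 0.483 / 0.487 SD |

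The stated pair (0.51 SD, 80%) falls at about 90 per group, a number the section does not mention.

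**Step 3. One-sided .01.** At 70 per group, power is 75.5% (t: 74.6%) and the detectable difference is 0.54 SD. Reaching 0.51 SD needs 78 per group (t: 79). A one-sided test does not recover the figure at 70.

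**Step 4. Correlation that would make 0.51 SD hold at 70 per group.** The variance must shrink by 0.51² / 0.585² = 0.2601 / 0.3422 = 0.76.
- Baseline-adjusted (ANCOVA), factor 1 − ρ²: ρ = √(1 − 0.76) ≈ 0.49.
- Change from baseline, factor 2(1 − ρ): ρ = 1 − 0.76/2 = 0.62.
- Mean of four follow-ups with equal correlations, factor (1 + 3ρ)/4: ρ = (4 × 0.76 − 1)/3 ≈ 0.68.

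**Step 5. Abstinence, 24% against 5%, two-sided .01, 70 per group.**
- Pooled z: [0.19 × √70 − 2.576 × √(2 × 0.145 × 0.855)] / √(0.24 × 0.76 + 0.05 × 0.95) = (1.590 − 1.283)/0.479 = 0.64, so power is 73.9%.
- Fisher's exact test: 70.9%.
- Arcsine: h = 0.573, and 0.573 × √35 − 2.576 = 0.81, so power is 79.2%.

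At 100 per group, pooled z gives 90.1%. If 24% and 5% are rates among those followed up, counting missing as smoking turns them into 0.7 × 24 = 16.8% and 0.7 × 5 = 3.5% of 100 per group, with 70.9% power.

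**The case against.** The strongest reply is that 70 per group need not be the base. The paragraph's subject is the 200 recruited; 70 per group stands in parentheses, and the sufficiency claim is about intention to treat. The rule "missing data will be classified nonabstinent or as failing to achieve reduction" keeps everyone randomised in those analyses. If 0.51 SD is an effect in all randomised, power at 100 per group is about 84%, so calling the sample sufficient is correct and slightly cautious. This stands as a possible reading. It does not yield the printed figure, since 100 per group would give about 0.49 SD.

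Second, the planned method is not an unadjusted comparison at one time point. Repeated-measures contrasts use within-person correlation, and Step 4 shows that plausible-looking values would bring 0.51 SD within reach at 70 per group. This also stands. A reader might infer that the trial's real power is 66%, but the documents do not support that: 66% holds only for an unadjusted two-sided comparison of 70 per group. Equally, the documents give no correlation that would support 80%. The correlations above are back-calculated, and the article does not say explicitly whether baseline is one of the occasions.

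Third, the wording is approximate, and power for abstinence is openly described as uncertain. The approximation covers differences between formulas (0.578 or 0.585), but it hardly covers a gap from 0.51 to 0.58 in a figure given to two decimals. The caution about abstinence does not extend to the continuous outcomes.

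**Conclusion.** The continuous-outcome figure is wrong as written, in a limited sense: on the inputs printed beside it, 0.51 SD at 80% power follows from neither 70 nor 100 per group. For 70 per group, unadjusted and two-sided, the detectable difference is about 0.58 SD, roughly 14% larger (0.58/0.51 = 1.14), and power for 0.51 SD is about 66%. The stated figure holds at 70 per group only with an unstated correlation of about 0.5 (baseline-adjusted) or 0.62 (change scores).

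A reader might also infer that the abstinence figure is miscalculated. That is not shown. At 70 per group it is met to within a percentage point by the arcsine method (79%), missed by pooled z (74%), and exceeded at 100 per group (90%). What it lacks is a stated base, which matters because missing is counted as nonabstinent: by pooled z, power is 90% if the rates apply to all randomised and 71% if they apply to those followed up.

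The calculations assume equal groups and two-sided testing.

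**What to change.** In *Sample size and detectable difference*, do one of the following:

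- state the continuous-outcome detectable difference as about 0.58 SD for the 70 per group expected at 6 months, with 80% power at two-sided .01; or
- keep 0.51 SD, name the baseline-adjusted or change-score analysis behind it, and give the assumed correlation (about 0.5 or 0.62 respectively, at 70 per group).

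In the same paragraph, say whether 24% and 5% are rates among all randomised or among those followed up, and which test the power refers to.

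The cost is one reworded paragraph. No extra participants are needed, and the design, outcomes and significance threshold stay as they are. Under the first option the stated sensitivity becomes slightly less favourable. Under the second, the *Analysis* section must specify the same adjusted analysis.
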